## **HYPOTHESIS**

We hypothesize that the integration of family planning services into HIV care and treatment will increase the utilization of all modern contraceptive methods, especially more effective contraception (MEC) (including oral, implantable, injectable, and intra-uterine methods), among HIV-infected women. Additionally, we hypothesize that by increasing the contraceptive prevalence, contraceptive compliance and continuation among HIV-infected women will increase and unintended pregnancy rates among HIV-infected women will decrease.

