## **SPECIFIC OBJECTIVES**

1. To compare the contraceptive prevalence among HIV-infected individuals receiving care at PSCs randomized to the integrated model to that of HIV-infected individuals at control (non-integrated) PSCs
2. To compare the proportion of pregnancies that are unintended among HIV-infected women receiving care at PSCs randomized to the integrated model to that of HIV-infected women at control (non-integrated) PSCs

3. To assess the feasibility and acceptability of integration of family planning into HIV care and treatment programs;
4. To evaluate knowledge of contraception and the importance of dual method use among HIV-infected women;
5. To better understand the pregnancy intentions of HIV-infected women and men who seek health care services in Migori, Rongo, Kisumu East and Suba Districts

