### **3. Part III: Post-intervention data collection (Months 7-15)**

#### **3.1. Post-intervention site-based data collection**

Over the following nine months, data on contraceptive prevalence, contraceptive methods used and pregnancy (including degree to which pregnancy was planned and desired) will be collected, as part of routine care, at the 18 sites (twelve intervention and six control sites) among women age 18-45 and men age 18 and older. Data will also be collected on whether contraceptive counseling was performed at each clinic visit. This information will be collected in the standardized clinic encounter form from all HIV-positive women and men at the time of each visit to the site. At each of the sites, a random sample of 10-15% of all charts will be reviewed during the post-intervention period to determine if the family planning module of the clinical encounter form is being filled out. A draft of the questions that will be used to collect the site-based data is included in Appendix A.

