### **ENDPOINTS**

**Primary Outcomes** (data abstracted from clinic encounter forms from all HIV-positive clients):

1. Contraceptive prevalence
  - a. Will compare post-intervention data from intervention sites to data collected over same time period from control sites
2. Pregnancy rate (number of pregnancies/number of unique clients seen during post-intervention data collection period) and percent of pregnancies that are unplanned
  - a. Will compare post-intervention data from intervention sites to data collected over same time period from control sites

**Secondary Outcomes** (data collected from KAP surveys and in-depth interviews):

1. Knowledge of contraceptive methods among HIV-positive clients
  - a. Will compare pre-intervention rates from baseline data to post-intervention data at intervention sites

- b. Will compare pre-intervention rates from baseline data to post-intervention data at control sites
  - c. Will compare post-intervention data from intervention sites to data collected over same time period from control sites
- 2. Knowledge of contraceptive methods among providers, including peer counselors, at HIV care and treatment centers
  - a. Will compare pre-intervention rates from baseline data to post-intervention data at intervention sites
  - b. Will compare pre-intervention rates from baseline data to post-intervention data at control sites
  - c. Will compare post-intervention data from intervention sites to data collected over same time period from control sites
- 3. Acceptability of family planning services
  - a. Will compare pre-intervention rates from baseline data to post-intervention data at intervention sites
  - b. Will compare pre-intervention rates from baseline data to post-intervention data at control sites
  - c. Will compare post-intervention data from intervention sites to data collected over same time period from control sites
- 4. Feasibility of providing family planning services at HIV care and treatment centers (data from post-intervention surveys of clinic staff)
- 5. Reproductive intentions of HIV-infected clients receiving care and treatment (data from baseline client surveys and in-depth interviews)

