## **STATISTICAL/ANALYSIS PLAN**

### **Sample size considerations**

**Data abstracted from clinical encounter forms.** We have used ACLUSTER program to generate the number of PSC pairs (or clusters) that we will need to assess changes in contraceptive prevalence and unintended pregnancy. The first input into this program is the size of each cluster (or the number of eligible subjects available at each PSC site). There are a total of 36 FACES-supported PSC sites in Migori, Rongo, Kisumu East and Suba Districts, which are not all equal in size. The first calculation takes into account how we determine the average number of non-pregnant females of reproductive age that are potentially recruitable at each site. The other main input is the desired effect size we aim to be able to measure. Additional inputs include alpha, power and the Intra-cluster Correlation Coefficient (a measure of how similar we expect the two sites in each paired cluster to be to each other, for which we selected an intermediate value). Based on this we need 18 sites, 12 with the intervention and 6 control to be able to evaluate the integration model we propose as described in more detail below.

For the main cluster-randomized trial, the following data were inputted into the ACLUSTER program to generate an estimated number of clusters needed:

- 1. Number of subjects per cluster or site
  - a. The eligible sample includes all FACES-supported PSCs in Suba, Kisumu East, Rongo and Migori Districts. The enrollment in December 2007 at the 16 FACES-supported sites in Suba District was 10,280, at the four sites in Kisumu was 6,593, at the five sites in Rongo was 1,338, and at the 11 FACES-supported sites in Migori District is 4,882.

- b. Because there are not accurate data about the number of non-pregnant women of reproductive age at these sites, we applied estimates based on observations of client demographics at the FACES site in Kisumu, where 65% of all clients are adult females, 89% of the female population is of reproductive age, and 90% of the reproductive age females are not pregnant.
  - c. Applying these estimates, our eligible sample is approximately 12,023 women at 36 sites, an average of 333 women per site. For the sample size calculation, a conservative estimate of approximately 200 eligible women per site was used to allow for inclusion of smaller sites.
- 2. Effect size on primary outcome.

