### **Data analysis plan**

Analyses of data from the study health facilities, given the randomized cluster design, will mainly be conducted at the cluster (health facility) level. Individual level analyses will take into account

cluster effects. Primary analyses will be based on the “intention to treat” (ITT) principle, with facilities randomized to the intervention group classified as delivering “integrated services” regardless of whether or not individual women actually received integrated services.

Preliminary analyses will be conducted to compute study outcome variables and to summarize characteristics of control and treatment sites to assess the effectiveness of randomization. Initial analyses also will involve inspection of the frequency distributions of variables to identify outlying or unusual values. Following univariate descriptions of the data, bivariate and multivariate associations will be assessed as described below.

Analysis of the primary outcomes, contraceptive prevalence and unintended pregnancy rates, and the secondary outcomes, acceptability of services and knowledge related to contraception, will be based on a comparison of means or proportions between study arms using a weighted t-test that accounts for correlations between individual outcomes within sites. Even though there are only 12 health facilities in the intervention arm and 6 health facilities in the comparison arm, each mean or percentage will be based on a relatively large number of women, and the normal approximation to the binomial distribution can be used. These tests will be evaluated based on a two-sided alternative hypothesis, 80% power, and a 5% type I error rate. The same basic approach will be used for the other primary and secondary outcomes. Results will be summarized as odds ratios for models based on binary responses (e.g. use of contraception or experiencing unintended pregnancy), and mean changes for continuous responses (e.g. score on knowledge test).

As noted above, All open-ended interviews will be tape recorded (if the woman gives informed consent), transcribed, translated to English. A content analysis will be performed using the qualitative software ATLAS.ti in order to describe themes in women’s experiences undergoing contraceptive counseling, receiving family planning methods and in the acceptability of these services.

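### The pregnancy primary outcome is stated as different quantities in different sections, and as written it counts pregnancies conceived before integration, which pulls any effect towards the null

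*Protocol*

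**What the plan says.** The Protocol describes this outcome in four places.

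- **Hypothesis:** "unintended pregnancy rates among HIV-infected women will decrease".
- **Specific Objectives, item 2:** "To compare the proportion of pregnancies that are unintended among HIV-infected women receiving care at PSCs randomized to the integrated model", against the control sites.
- **Endpoints, Primary Outcomes, item 2:** "Pregnancy rate (number of pregnancies/number of unique clients seen during post-intervention data collection period) and percent of pregnancies that are unplanned". The line heading both primary outcomes gives the source as "data abstracted from clinic encounter forms from all HIV-positive clients".
- **Data analysis plan:** "Analysis of the primary outcomes, contraceptive prevalence and unintended pregnancy rates". The same section names the experience of an unintended pregnancy as an example of a binary response to be summarised by odds ratios.

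On who contributes, section 3.1 says the post-intervention data are "collected in the standardized clinic encounter form from all HIV-positive women and men at the time of each visit". Study population/Study subjects describes the women as non-pregnant, and Sample size considerations, item 1b, applies the estimate that "90% of the reproductive age females are not pregnant" to count eligible women. Sections 1.1 and 3.1, the consent section for site-based data and the Endpoints do not carry that condition. The client surveys and open-ended interviews do list it as an inclusion criterion.

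**The concern.** A primary outcome should be one quantity. Here a reader can take the numerator as all pregnancies or as unintended ones, and the denominator as clients, women or pregnancies. The choice can decide the conclusion. Expected Application of Results makes introduction at all supported clinics depend partly on whether unintended pregnancies fall, and neither component of the endpoint is, on its own, that quantity.

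There is also a timing problem. A woman already pregnant when the post-intervention window opens attends during it and is recorded as pregnant. Nothing in the endpoint removes her, although better access to contraception could not have prevented a pregnancy that began before integration. Such pregnancies are expected equally in both arms, so they do not create a false effect; they shrink a real one.

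**Working it through.** **1. The quantities side by side.** Let U and I be unintended and intended pregnancies, N women and C clients.

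| Section | Quantity |
|---|---|
| Hypothesis; Data analysis plan | U/N |
| Specific Objective 2 | U/(U+I) |
| Endpoints | (U+I)/C, and U/(U+I) |

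**2. The plan's own count of women.** The listed enrolment is 10,280 + 6,593 + 1,338 + 4,882 = 23,093. Then 23,093 × 0.65 × 0.89 × 0.90 = 12,023, the stated eligible sample. The last factor removes pregnant women, so the sample size section assumes the restriction that the endpoint omits.

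**3. Share of counted pregnancies conceived before integration.** Assume a constant conception rate, pregnancies lasting D months and a window of W months. Pregnancies in progress at the start are proportional to D, and those arising in the window to W.

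- Effect from month 7 (window opens): share s = D/(D+W).
- Effect from month 4 (Part II covers months 4-6): s = (D−3)/(D+W).

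W is 9 by section 3.1. It is 8 by the Time Frame table, where data collection runs from April to November 2009 and overlaps implementation in April-May. D = 6 to 9 is an assumption.

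| D | W | Effect from month 7 | Effect from month 4 |
|---|---|---|---|
| 6 | 9 | 6/15 = 40% | 3/15 = 20% |
| 9 | 9 | 9/18 = 50% | 6/18 = 33% |
| 9 | 8 | 9/17 = 53% | 6/17 = 35% |

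The range is about 20% to 53%. Delay between conception and recognition is ignored; allowing for it would raise the share.

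**4. Dilution.** Let u be the unintended share without the intervention and RR the true ratio for unintended conceptions, with intended conceptions unchanged.

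- Counted unintended ratio: s + (1−s)RR
- All-pregnancy ratio: s + (1−s)(1−u+u·RR)
- Percent unplanned: u × (first)/(second)

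Assume u = 50%. The Background reports over 50% of births unintended, many to women of unknown HIV status.

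| RR | s | Counted unintended ratio | All-pregnancy ratio | Percent unplanned (from 50%) |
|---|---|---|---|---|
| 0.8 | 0 | 0.80 | 0.90 | 44.4% |
| 0.8 | 0.20 | 0.84 | 0.92 | 45.7% |
| 0.8 | 0.53 | 0.91 | 0.95 | 47.5% |
| 0.5 | 0 | 0.50 | 0.75 | 33.3% |
| 0.5 | 0.20 | 0.60 | 0.80 | 37.5% |
| 0.5 | 0.53 | 0.77 | 0.88 | 43.3% |

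**5. Percent unplanned on its own.** It conditions on pregnancy, which the intervention is meant to change. With s = 0 and RR = 0.8 it is 0.40/(0.40+0.50) = 44%. If both kinds fall by 20% it is 0.40/(0.40+0.40) = 50%, so it shows nothing although U/N has fallen.

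**6. Men in the denominator.** If f is the female share and p the rate in women, the rate per client is f·p. Take p = 20% as an illustration (10% pregnant at a point in time plus an assumed 10% conceiving in nine months). With equal numbers of men and women, as in the planned 2,520 of each, it reads 10%. Mixes of 60% and 70% female give 12% and 14% with no true difference. If f is equal in both arms it cancels, and the rate ratio is unchanged.

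**The case against.** Several points on the other side have weight.

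- **The endpoint is a pair.** Pregnancy rate times percent unplanned gives unintended pregnancies per client, and the Data analysis plan treats an unintended pregnancy as a person-level binary response. A reader might infer that the endpoint cannot detect the hypothesised effect or would hide it. The documents do not support that: if both kinds of pregnancy fall together, the percentage stays flat but the paired rate falls. What stands is that no section specifies the product, and the product would still include earlier conceptions.
- **Men are probably not meant.** Sample size considerations gives men their own primary outcome, the Hypothesis and Objective 2 speak of women, and the Data analysis plan justifies its approximation by the number of women. It is also tempting to take the 65% adult-female figure as meaning that 35% of the denominator is male. That figure describes all clinic clients, so the remainder may include children, whereas the site data cover adults. What stands is that the Endpoints wording does not exclude men.
- **Pregnant women may be meant to be excluded.** Two sections say non-pregnant, so a large share of earlier conceptions is not established as the intention. It follows from the endpoint and section 3.1 as written, and the sections contradict each other.
- **Detail may come later.** The Protocol promises a detailed analysis plan, and person-time rules commonly sit there. Such a plan can refine one outcome; it should not have to choose between quantities that the Protocol states differently.
- **The trial is sized on contraceptive prevalence.** True, so that sample size is not affected by this point.

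**Conclusion.** The point holds as an inconsistent and badly bounded primary outcome. The sections name different quantities, and the endpoint as written lets in pregnancies that integration could not have prevented. The direction, towards no effect, needs no assumption beyond such pregnancies being counted. The size does: 20% to 53% of counted pregnancies depends on assumed duration, window length and onset of effect. At u = 50%, a true 20% fall in unintended conceptions would then appear as a 9% to 16% fall in counted unintended pregnancies and a 5% to 8% fall in all pregnancies. A reader might infer that about half of the counted pregnancies certainly pre-date integration. That requires the effect to start only at month 7, and it ignores conceptions during months 4-6, when integration is being put in place. The question of men is an ambiguity to close; it is not a demonstrated bias in the rate ratio.

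**What to change.** Use one definition in Specific Objective 2, the Endpoints and the Data analysis plan: new unintended pregnancies during the post-intervention window among women aged 18-45 recorded as not pregnant at their first visit in that window, with the same calendar window in both arms. The denominator is those women, or their woman-time if visit follow-up differs between sites or arms. Reconcile Study population and section 3.1 with this, and the window in section 3.1 with the Time Frame table. Report percent of pregnancies unplanned descriptively.

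The change is wording, since pregnancy and its planning are already recorded at each visit. Two costs remain. Fewer events are counted. Some early pregnancies unrecognised at the first visit will still enter unless last menstrual period is available; Preliminary data mentions a space for it only on the intake form, and section 3.1 does not list it among the visit data.

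Losing events need not lose power. Take RR = 0.5, u = 50%, 10% of women conceiving in nine months, 140 women at each of 6 control and 12 intervention sites, and an intra-cluster correlation of 0.01 (design effect 1 + 139 × 0.01 = 2.39). The new outcome, 5.0% against 2.5%, then has power of about 0.48. All pregnancies per woman, 20.0% against 17.5%, has about 0.16. These inputs are partly assumed, and both values fall short of 0.8.

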#### **3.2. End-of-study KAP survey of female and male clients**

In the final three months of the study, a convenience sample of approximately 28 female clients and 28 male clients will be recruited from each of 18 sites (N=488 female and 488

male patients). All 976 participants will complete the family planning KAP survey that was used at baseline with additional questions about the acceptability of family planning services offered at the site. Note that some of these participants may have also participated in the baseline KAP survey. The final version of the survey will be submitted to the IRB prior to initiating data collection.

The survey will be administered face-to-face by an interviewer in the respondent's preferred language in a private area of the centre. Inclusion criteria for the client KAP survey will be: 1) HIV-positive woman or man obtaining care at the FACES site, 2) not currently pregnant (if female), 3) age 18 to 45 years old if female and age 18+ if male; and 4) willing and able to give informed consent. Participants will be excluded if they do not meet the inclusion criteria listed above. Participants will be reimbursed a maximum of USD\$3 (approximately 200 Kenyan Shillings at current exchange rate) for transport.

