  - a. The primary outcome upon which we based our sample size calculation is contraceptive prevalence. According to the 2003 Kenya Demographic and Health Survey, approximately 22% of women in a union in Nyanza Province use a modern contraceptive method. This level of contraceptive prevalence is similar to that seen among clients at the FACES sites. We would like to be able to detect a 8% rise in contraceptive prevalence to 30%.
- 3. Assumptions
  - a. Two-sided alpha of 0.05
  - b. Power of 0.8
  - c. Intra-cluster Correlation Coefficient of 0.01
- 4. Sample size.
  - a. Using these estimates, the needed sample size is approximately 140 women at each of the 18 sites, for a total sample of 2,520 women.
  - b. We plan to initially recruit a similar number, 2,520, of male clients, however our primary outcome for men will be the proportion of male clients who report they or their partner are interested in starting a new FP method after receiving FP counseling during their visit. In order to accurately calculate this sample size, baseline data is needed to estimate the baseline proportion of male clients who would express interest in starting a new FP method. Thus, after the baseline data collection phase a more accurate sample size for male clients will be calculated.

**KAP surveys.** Because the largest sample sizes are required for expected proportions nearer to 0.5 than to 0 or 1, we will take the worst-case scenario and assume that for each individual question on the survey approximately half of the participants will answer correctly. We hypothesize that people in the intervention sites will be more knowledgeable after the intervention at the end of the study, so we would like to test for at least a ten percentage point difference in correct answers among patients in the intervention sites (~60% correct) compared to patients in the comparison sites (~50% correct), as well as a 10% increase in correct answers among patients in the intervention sites compared to the baseline results. For a one-sided test of two proportions using two samples, power of 0.8, and an alpha level of 0.05, the required sample size is 325 patients from the intervention sites and 163 patients from the comparison sites for both men (N=488) and women (N=488).

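### For knowledge and acceptability, the within-arm before-after comparisons should be descriptive: a change shared by both arms can make the integration-arm rise significant with no effect of integration

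*Protocol*

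**What the plan says.** In the protocol's Endpoints section, secondary outcomes 1 to 3 (client knowledge, provider knowledge, acceptability) each carry the same three comparisons:

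- Item a is a before-after comparison within one arm: "Will compare pre-intervention rates from baseline data to post-intervention data at intervention sites".
- Item b repeats that before-after comparison inside the control arm.
- Item c is the concurrent, randomised one: "Will compare post-intervention data from intervention sites to data collected over same time period from control sites".

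None is labelled descriptive. The primary outcomes in the same section use only the concurrent comparison.

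Under Sample size considerations, the KAP paragraph sets a between-arm target (about 60% correct against 50%) and adds a second one: "as well as a 10% increase in correct answers among patients in the intervention sites compared to the baseline results". The calculation is one-sided at alpha 0.05 with 80% power. Its result, which applies to each sex, is that "the required sample size is 325 patients from the intervention sites and 163 patients from the comparison sites".

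The Data analysis plan bases the analysis of acceptability and knowledge on a weighted t-test between the arms, two-sided at 5%.

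Two other places bear on the point. Section 2.2 adds a family planning module to the encounter form at intervention and control sites alike. Section 3.2 reuses the baseline questionnaire and says: "Note that some of these participants may have also participated in the baseline KAP survey".

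**The concern.** A before-after test inside one randomised arm has no concurrent control. Between the two surveys, scores can rise for reasons that have nothing to do with integration. The new module prompts discussion of contraception at every site, some clients answer the same questionnaire twice, and background knowledge may be changing. For staff, section 3.3 tries to re-interview the same people on the same topics. Test a credits all of this to integration.

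Reading a beside b does not repair it. The client samples are 325 and 163 per sex, so the same true rise is more likely to reach significance at integrated sites than at control sites. A report that knowledge improved where services were integrated but not elsewhere would look like an effect when it may only reflect unequal sample sizes. Knowledge and acceptability are specific objectives 3 and 4, and acceptability is one of the considerations for roll-out under Expected application of results.

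**Working it through.** **Inputs from the protocol.** 50% correct as the reference; 325 intervention and 163 control clients per sex and round; alpha 0.05. The KAP sizing is one-sided and the Data analysis plan two-sided, so both are shown. **Assumption.** The protocol gives no size for a shared trend, so equal rises of 3, 5, 8 and 10 points in both arms are tried, with no integration effect. Clustering is ignored at first, as in the KAP sizing.

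**1. The plan's own figure.** For 50% against 60%, 1:1, one-sided, 80% power:

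n = [1.645·√(2·0.55·0.45) + 0.842·√(0.25 + 0.24)]² / 0.10² = 305 per group.

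With continuity correction: 305/4·[1 + √(1 + 4/(305·0.10))]² = 325. So 325 is the per-group size of an equal-group test, and 163 is half of it, rounded up. The 2:1 between-arm comparison on the same basis needs 486 + 243 = 729, so 325 + 163 = 488 does not reproduce as a size for c. At the stated sizes, a (325 v 325) has 82% power one-sided and c (325 v 163) has 68% (two-sided 73% and 56%). The uncontrolled test is the better powered of the two.

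**2. Probability that a within-arm test is significant under a shared rise d.**

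P = Φ[(d − z·s0)/s1], with s0 = √(2·p̄(1 − p̄)/n), p̄ = 0.50 + d/2, and s1 = √{[0.25 + (0.5 + d)(0.5 − d)]/n}.

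Example, d = 0.10, one-sided:
- a, n = 325: (0.10 − 1.645·0.03903)/0.03883 = 0.922, P = 0.82
- b, n = 163: (0.10 − 1.645·0.05511)/0.05483 = 0.170, P = 0.57
- a significant and b not: 0.822·(1 − 0.568) = 0.36

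| Shared rise | a, one-sided | b, one-sided | a yes, b no | a, two-sided | b, two-sided | a yes, b no |
|---|---|---|---|---|---|---|
| 3 points | 0.19 | 0.13 | 0.16 | 0.12 | 0.08 | 0.11 |
| 5 points | 0.36 | 0.23 | 0.27 | 0.25 | 0.15 | 0.21 |
| 8 points | 0.66 | 0.42 | 0.38 | 0.53 | 0.30 | 0.37 |
| 10 points | 0.82 | 0.57 | 0.36 | 0.73 | 0.44 | 0.41 |

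The reverse pattern (b significant, a not) has probability 0.10 to 0.15 at 8 to 10 points, so the asymmetry favours integration.

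**3. Clustering.** If the main trial's ICC of 0.01 held for the survey items with 28 clients per site (an assumption), the design effect would be 1 + 27·0.01 = 1.27. Dividing the sample sizes by 1.27, the two-sided pattern probability is 0.33 at 8 points and 0.40 at 10.

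**4. Comparison c under the same trend.** Both arms have the same true post-intervention rate, so the null hypothesis is true and the test rejects at its nominal level, provided it accounts for sites as the Data analysis plan says.

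**5. Power of an unadjusted difference in change** (50% to 60% against 50% to 50%, rounds treated as independent):

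SE = √(0.25/325 + 0.24/325 + 0.25/163 + 0.25/163) = 0.0676

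Power = Φ(0.10/0.0676 − 1.645) = 0.43 one-sided; Φ(0.10/0.0676 − 1.960) = 0.32 two-sided. The figures for c in step 1 are 0.68 and 0.56.

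**The case against.** The strongest reply is that the protocol already contains the right test. Item c is concurrent and randomised, so it controls for a common time trend, and the Data analysis plan makes a between-arm test the basis for these outcomes. A reader might infer from items a and b that the plan has no comparison free of time trends. The documents do not support that.

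Four further limits stand.

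- Item b involves no integration and cannot be taken for its effect. It can even expose a shared trend. Only a, or a read against b, can mislead.
- A reader might infer that objectives 3 and 4 would be declared met on a significant a with a non-significant b. No such rule is written: the objectives speak of assessing and evaluating, and the roll-out section ties acceptability to no test.
- The size depends on the assumed trend. At 3 to 5 points the misleading pattern falls to 11 to 27%. The month numbering puts about a year between surveys, but the Time frame table shows a shorter gap for clients (baseline to February-March 2009, follow-up June to September 2009).
- The 325 and 163 argument covers client surveys only. Provider knowledge rests on some 30 to 45 staff.

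The reply does not dispose of the point. The KAP sizing still names the item a rise as an effect to be tested, which does not agree with the Data analysis plan's between-arm basis, and nothing marks a and b as descriptive.

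**Conclusion.** The concern holds in a limited form. For secondary outcomes 1 to 3, test a cannot separate integration from changes shared by both arms, and setting it beside b does not help when the control sample is half the size. With no integration effect and an assumed common rise of 3 to 10 points from 50%, a is significant with probability 0.19 to 0.82 one-sided (0.12 to 0.73 two-sided). The contrast of a significant and b not appears for about 16 to 38% of client-survey items (11 to 41% two-sided), before any design effect. These figures rest on the assumed trend, the normal approximation, and the two arms' tests being independent given that trend. Item c is unaffected, and the primary outcomes do not use before-after tests. Severity is modest: the remedy is to state clearly which comparison carries the inference.

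**What to change.** - **Endpoints, secondary outcomes 1 to 3:** label a and b descriptive, reported as estimates without p-values. Rest inference on c, adjusted for the site's baseline value of the same measure.
- **Sample size considerations, KAP surveys:** delete the integration-arm rise over baseline as a target to be tested, so that this section agrees with the Data analysis plan.
- **Do not substitute an unadjusted difference in change.** At 325 and 163 it has only about 43% power one-sided (32% two-sided). Reaching 80% would take about 921 + 461 clients per sex and round one-sided, or 1,170 + 585 two-sided, before any design effect.

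The cost is a change of wording. Baseline and follow-up surveys are already planned at the same 18 sites, so no new data are needed. What is given up is a stand-alone before-after claim for the integrated sites.
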